## Abstract

**Background:**

Patients with a first episode psychosis (FEP) who are admitted for the first time to a psychiatric hospital frequently have experienced prior psychological trauma. Additionally, 40–80% develop posttraumatic stress symptoms, which are summarized as a post-psychotic post-traumatic syndrome (PPS). Eye Movement Desensitization and reprocessing (EMDR) therapy could be an effective psychotherapy to treat a PPS and prior psychological traumas in this population.

**Objectives:**

To assess if EMDR therapy leads to: 1) a reduction of relapses after intervention, 2) an improvement of trauma-related, psychotic and affective symptoms, 3) an improvement of overall functioning, and 4) an improvement in quality of life.

**Methods:**

This is a multicenter phase II rater-blinded randomized controlled trial in which 80 FEP patients with a history of psychological trauma will be randomly assigned to EMDR (n = 40) or to TAU (n = 40). Traumatic events will be measured by the Global Assessment of Posttraumatic Stress Questionnaire, the Cumulative Trauma Screening, the Impact of Event Scale-Revised, the Dissociative Experiences Scale, the Childhood Trauma Scale, the Holmes–Rahe Life Stress Inventory, and the Dissociative Experiences Questionnaire. Clinical symptomatology will be evaluated using the Suicide and Drug Consumption module of the International Neuropsychiatric Interview, Structured Clinical Interview for Positive and Negative Syndrome Scale, Young’s Scale for Mania Evaluation, and Beck Depression II Questionnaire. Functionality will be assessed with the Global Assessment of Functioning and the Quality of Life with the Standardized Instrument developed by the EuroQol Group. The cognitive insight and adherence to the treatment will be assessed with the Beck Cognitive Insight Scale and the Drug Attitude Inventory. All variables will be measured at baseline, post-treatment and at 12-month follow-up.

**Conclusion:**

This study will provide evidence of whether EMDR therapy is effective in reducing trauma and clinical symptoms, reducing relapses and in improving functionality and quality of life in patients with FEP and a history of trauma.

**Clinical Trial Registration:**

www.ClinicalTrials.gov, identifier: NCT03991377

## Introduction

Outcomes in patients with schizophrenia spectrum disorders and bipolar disorder have remained suboptimal (1, 2). One factor contributing to this is the high prevalence of psychological trauma and adverse life events in psychosis sufferers, nearly four times the rate in the general population (3). Evidence suggests traumatic life events are an important environmental factor implicated in an increased risk for the onset of a range of psychotic spectrum disorders, including first episode of psychosis (FEP) (4, 5) and affective psychosis in bipolar disorder (6). Additionally, psychological trauma in patients with psychosis is associated with poorer service engagement (7), worse outcomes in the form of longer stays in hospital and more frequent readmissions (8), more severe positive psychotic symptoms (9), and increased suicidal ideation (10).

The physiopathological mechanisms underlying the link between trauma and psychosis are not fully understood, but appear to be due to a complex interplay of trauma, genetic, epigenetic and environmental factors (4). Furthermore, the prevalence of posttraumatic stress disorder (PTSD) in psychosis was estimated at 12.4% in a meta-analysis of 20 studies (95% CI, 4.0–20.8%) (11). A diagnosis of PTSD in psychosis was associated with poorer social functioning and more severe psychiatric symptoms (12–14). Of particular note is that the experience of suffering a FEP in and of itself can constitute a highly stressful event which triggers symptoms compatible with PTSD: this clinical condition has been defined as post-psychotic post-traumatic syndrome (PPS) (15) and is estimated to occur in 40–80% of all FEP patients (16). A range of issues are potentially traumatic for FEP patients, from the experience of suffering psychotic symptoms, such as auditory hallucinations involving hearing voices, persecutory delusions or disorganized behavior, to the experience of being admitted to a psychiatric unit for the first time. This experience can involve involuntary hospitalizations and/or drug treatment, or other restrictive measures such as mechanical restraints, and is an important risk factor for traumatization (10), and is associated with feelings of anger, sadness, distrust or impotence. The risk of developing PPS following a FEP is increased in patients with prior childhood trauma (17). The presence of PPS is associated with an increased severity in psychotic symptoms (18) and concomitant clinical depression (19). Trauma hinders adherence to drug treatment (20), which is already particularly difficult in FEP patients in general (21). Thus, PPS has significant consequences at both prognostic and treatment levels (15).

All of this evidence suggests there is an urgent need to go beyond the treatment of psychotic symptoms and integrate trauma-focused psychotherapy into the care plan for FEP patients, especially in the high-risk period following hospitalization.

Eye movement desensitization and reprocessing therapy (EMDR) is a psychotherapy based on standardized protocols, which integrates the use of bilateral stimulation (such as side-to-side eye movements) with elements of cognitive-behavioral, interpersonal and body-centered therapies (22). EMDR has been integrated into the World Health Organization guide as a first-line psychotherapy for the treatment of PTSD in adults, children and adolescents (for a review, see (23). Despite the high prevalence of comorbid PTSD in psychosis and the strong empirical evidence supporting the efficacy of this therapy, patients affected by psychosis have been commonly excluded from clinical trials related to trauma (24). However, this tendency has begun to change and early evidence shows that positive and affective symptoms in severe psychiatric disorders, as well as comorbid trauma-related symptoms, can be ameliorated by EMDR therapy (25, 26). A randomized controlled multicenter study has been conducted by (25), with a sample of 155 patients with chronic psychosis and comorbid PTSD. The results of this study demonstrated the efficacy of EMDR in the treatment of chronic PTSD symptoms in patients with a lifetime diagnosis of psychosis, with the therapeutic benefits maintained at the 6-month follow-up and a reduction in adverse events and revictimization. Several sub-analyses of the same study have demonstrated the efficacy of EMDR therapy also in patients with greater dissociative symptoms (27), with psychotic symptoms, depression and social functioning (25), and also a cost-effectiveness study in favor of EMDR therapy when compared to prolonged exposure (28).

Therefore, the main objective of the study is to evaluate the efficacy and safety of EMDR therapy in patients with an affective or non-affective FEP in the reduction of relapses, as well as the improvement of clinical symptoms, its possible positive impact on functioning and adherence to pharmacological treatment.

## Methods

### Design and Study Setting

This multicenter phase II rater-blinded randomized controlled trial will involve the participation of four different centers in Catalonia: Hospital Parc de Salut Mar, Vic Hospital Consortium, University Hospital Mutua of Terrassa and Althaia Xarxa Assistencial Universitària of Manresa. The Hospital Parc de Salut Mar is a center of reference for mental health treatment and research, among other disciplines, and the collaboration with the rest of the institutions will ensure the recruitment of the complete sample.

Participants will be randomized to either treatment as usual (TAU) or to 20 individual 60-minute EMDR sessions over 5 months, as well as TAU. EMDR therapists participating in this trial are highly experienced, have received advanced training in EMDR protocols, and were recruited through face-to-face interviews. Assessments will be carried out at three time points: baseline (T0), post-treatment at 6 months (T1) and at 12-month follow-up (T2) (see **Table 1**). The clinical raters carrying out evaluations will be blind to the participants’ research condition; however this is not a double-blind study as it is not possible to mask from the patient whether they are undergoing EMDR therapy or not due to its use of bilateral stimulation.

**Table 1 T1:** SPIRIT Flow diagram: Schedule of enrolment, interventions and assessments.

Timepoint**	Study Period			
	Enrolment	Allocation	Post-allocation	Close-out
*-t_1_ & t_0_*	0	*T_1_*	*T_2_*
**Enrolment:**			
Eligibility screen	X			
DSM-V criteria for substances	X			
TAP	X			
BDI-II	X		X	X
YMRS	X		X	X
PANSS	X		X	X
EGEP-5	X			
CTQ	X			
CTS	X			
IES-R	X		X	X
H-RLSI	X			
SUD	X		X	X
DES	X		X	X
SDQ-20	X		X	X
Informed consent	X			
**Allocation**		X		
**Interventions:**				
EMDR				
TAU				
**Assessments:**				
GAF	X		X	X
EQ-5D	X		X	X
BCIS	X		X	X
DAI	X		X	X

DSM-V, Diagnostic and Statistical Manual of Mental Disorders, Fifth Edition; TAP, World Accentuation Test; BDI-II, Beck Depression Inventory; YMRS, Young Mania Rating Scale; PANSS, Positive and Negative Syndrome Scale; EGEP-5, Global Post-Traumatic Stress Assessment; CTQ, Childhood Trauma Questionnaire; CTS, Cumulative Trauma Scale; IES-R, Scale of the impact of events reviewed; H-RLSI, The Holmes-Rahe Life Stress Inventory; SUD, Subjective Unit of Discomfort; DES, Scale of Dissociative Experiences; SDQ, Somatoform Dissociation Questionnaire; EMDR, Eye movement desensitization and reprocessing therapy; TAU, Treatment as usual; GAF, Global Assessment of Functioning Scale; EQ-5D, Standardized Instrument for Evaluating Quality of Life Associated with Health developed by the EuroQol group; BCIS, Beck Cognitive Insight Scale; DAI, Drug Attitude Inventory.

The study has been approved by the Ethic Committees of the IMIM, Parc de Salut Mar (2018/7940/I), Vic Hospital (AC 269), Hospital Mútua of Terrassa, and Althaia Xarxa Assistencial Universitària of Manresa. All study subjects will sign the informed consent before they can enroll in the study. Further details of the trial design can be also gathered from **Supplementary Material** (Standard Protocol Items: Recommendations for Interventional Trials [SPIRIT] Checklist). The trial has been registered at ClinicalTrials.gov, identifier: NCT03991377.

### Study Aim

The main outcome of this project is to analyze whether EMDR therapy, as an adjuvant to TAU, is effective in reducing relapses in patients with an affective or non-affective FEP and a history of comorbid psychological trauma associated with first hospital admission and/or previous stressful life events. A range of scales, highlighted below, will be used to determine changes in psychiatric symptoms (see *Instruments and Measures*).

The secondary outcome includes whether EMDR therapy, as an adjuvant to TAU, is effective in reducing psychiatric symptoms and post-traumatic stress symptoms, in improving the overall functionality and quality of life associated with health, as well as adherence to pharmacological treatment. A range of clinical scales will be used the evaluate changes from baseline (see *Instruments and Measures*).

### Hypotheses

1. Patients in the EMDR group will show fewer relapses compared to the control group after therapy (T1) and at the 12-month follow-up visit (T2).2. Patients in the EMDR group will show fewer psychiatric and trauma-related symptoms compared to the control group after therapy (T1) and at the 12-months follow-up visit (T2).3. Patients in the EMDR group will improve their functional capacity in comparison to the control group at evaluations after therapy (T1) and at the 12-months follow-up visit (T2).4. Patients in the EMDR group will show a better adherence to pharmacological treatment in relation to the control group after therapy (T1) and at the 12-month follow-up visit (T2).

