### Computation of Sample Size

The study aims to assess the relative efficacy of an EMDR intervention protocol for patients with FEP versus TAU mainly in terms of stabilization and clinical improvement, reduction of anxious, depressive, somatic and/or psychotic symptoms, among others. For this reason, the main variable used is the number of clinical relapses after the intervention, with a follow-up of up to 12 months. Using previous studies as a basis (33), the sample size has been calculated based on a survival analysis with the statistical package “powerSurvEpi” for R, (http://www.r-project.org/) using an alpha = 0.005 instead of 0.05 to allow correction for multiple comparisons. The number of patients required to detect a hazard ratio = 2 in a Cox regression with a statistical power of 80% and alpha = 0.005 is n = 36 per intervention group (two groups, total n = 72). According to Chambless and Hollon (29), a sample of this size should show clinically relevant differences. Assuming a loss percentage of approximately 10–15% of the patients in the study, it would be necessary to recruit approximately 80 patients, 40 for each branch of intervention.

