### Statistical Analysis

The distribution of socio-demographic, clinical (including psychological trauma), functionality, quality of life and treatment adherence characteristics among baseline groups will be analyzed using descriptive statistics. Continuous variables with a normal distribution will be analyzed with the Multivariate Variance Analysis. The change of the clinical variables of functionality and quality of life with respect to the baseline assessment at strategic points of the intervention will be analyzed by ANOVA with repeated measurements, including time factors, treatment conditions and their interaction. For those cases in which the premises of normality are not fulfilled, the Wilcoxon test will be used. The differences between groups, for the categorical and main clinical variables, will be analyzed by means of the Chi-square test. Those variables that are statistically significant can be used as covariates for a logistic or linear regression study of the factors associated to the magnitude of the effect and determine which variables are the best predictors of functioning. The effect size index (Hedges g or r de Pearson index) will be estimated in case of correlation indexes of each of the analyses performed. The statistical software used for the analyses will be the latest available version of the SPSS (v. 23).

For the main statistical analysis, we will conduct an intention-to-treat (ITT) analysis. We will impute lost to follow-up with the Last Observation Carried Forward (LOCF) method.

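### The main relapse comparison is stated in three forms that do not agree; read literally, hypothesis 1 requires success at two visits, which the single-comparison sample size does not cover

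*Protocol article*

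**What the plan says.** All references are to the protocol article.

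- **Study Aim** makes relapse the main outcome, asking whether EMDR added to usual treatment "is effective in reducing relapses in patients with an affective or non-affective FEP". It gives no time point.
- **Hypotheses**, item 1, gives two: "Patients in the EMDR group will show fewer relapses compared to the control group after therapy (T1) and at the 12-month follow-up visit (T2").
- **Computation of Sample Size** gives one variable: "the main variable used is the number of clinical relapses after the intervention, with a follow-up of up to 12 months". It adds that "the sample size has been calculated based on a survival analysis with the statistical package" powerSurvEpi, "using an alpha = 0.005 instead of 0.05 to allow correction for multiple comparisons". The stated number is that "required to detect a hazard ratio = 2 in a Cox regression" with 80% power: 36 per arm, 72 in total, raised to 80 for losses.
- **Statistical Analysis** says: "The differences between groups, for the categorical and main clinical variables, will be analyzed by means of the Chi-square test". It names no visit for this test, does not mention Cox regression and does not repeat 0.005. It then states an intention-to-treat main analysis.
- **Design and Study Setting** places EMDR over 5 months, T1 at 6 months and T2 at 12 months.
- **Dropouts and Follow-Up** treats a patient admitted for relapse during the 5-month intervention as a dropout, excluded from the trial.

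**The concern.** A primary analysis needs one contrast, one method and one significance level. Here the hypothesis, the sizing and the analysis section each describe the relapse comparison differently, and no sentence ranks them. The conflict lies in what the article states, so it is not merely detail deferred to a fuller document.

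Two things are at stake. If hypothesis 1 is applied as worded, the trial must succeed at T1 and at T2, although the sample size was computed for one comparison. And if EMDR works, the two visits can easily give different verdicts in a trial of this size, with no rule for reading them. T1 is the weaker visit in any case. The sizing variable counts relapses after the intervention, which leaves about one month before T1, and the dropout rule removes patients admitted for relapse before that.

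**Working it through.** **1. The plan's own figure.** Events needed for a 1:1 comparison (Schoenfeld): 4(z₁₋α/₂ + z₀.₈)² / (ln HR)². With two-sided alpha 0.005 and HR 2: 4(2.807 + 0.842)² / 0.693² ≈ 110.8, so 111 events. Freedman's formula gives 120; one-sided versions give 98 and 106. All exceed 72 patients, so 72 is not reproduced at 0.005. That is a separate problem. What matters here is that the calculation covers one comparison, not a requirement to win twice.

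**2. Inputs for the two-visit check.**
- From the article: 40 per arm; T1 at 6 months and T2 at 12 months (both taken as timed from baseline); intervention 5 months; HR 2, that is 0.5 for EMDR against control.
- Assumed, because the article gives no relapse risk: 12-month relapse under usual treatment of 30%, 40% or 50%, and constant hazard.
- Test: uncorrected chi-square on cumulative relapse at each visit, two-sided, 200,000 simulated trials per setting.

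**3. Countable events at T1.** Monthly hazard λ = −ln(1 − p)/12. For p = 30%, λ = 0.0297. If relapses before month 5 are excluded, expected control events at T1 are 40·e^(−5λ)·(1 − e^(−λ)) = 34.5 × 0.0293 ≈ 1.0; the EMDR arm at half the hazard gives about 0.5. For p = 50% the figures are about 1.7 and 1.0. The T1 comparison would then rest on roughly 2 to 3 events in the whole trial.

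**4. Power, true HR 0.5, each test at 0.05.**

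| Counting rule | Control relapse at 12 months | T1 alone | T2 alone | Both visits |
|---|---|---|---|---|
| From randomisation | 30% | 19% | 31% | 14% |
| | 40% | 24% | 39% | 18% |
| | 50% | 30% | 49% | 24% |
| Relapses before month 5 excluded | 30% | 1% | 19% | 1% |
| | 40% | 3% | 24% | 2% |
| | 50% | 5% | 29% | 3% |

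The lower block removes every relapse before month 5. The rule names only relapses with hospital admission, so this block is the extreme case.

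At 0.005 per test, counting from randomisation, power is 1.5% to 5% for both visits, against 7.5% to 18% for T2 alone.

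**5. Disagreement between visits** (one significant, the other not), counting from randomisation: 23% to 30% of trials at 0.05 and 7% to 16% at 0.005 when HR is 0.5. With no true effect it is about 7% to 8% at 0.05 and below 1% at 0.005.

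**6. Error if success at either visit counted.** Upper figure if the tests were independent: 1 − 0.95² = 0.0975 at 0.05, and 1 − 0.995² = 0.009975 at 0.005. The visits share events, so the simulated values at 40 per arm are 0.085 to 0.091 at 0.05 and 0.008 to 0.009 at 0.005.

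**The case against.** The strongest reply is that the sample-size section already answers the question: one main variable, follow-up to 12 months, one Cox regression. That largely stands. A reader might infer that nothing indicates which time point decides, and the article does not support that. It points to 12 months; the fault is that hypothesis 1 and the analysis section do not follow.

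A reader might also infer that the trial could be declared positive on either visit at nearly double the nominal error. The article does not support this either. Hypothesis 1 joins the visits with *and*, and the sizing section adopts 0.005 expressly for multiple comparisons. At that level even an either-visit rule stays below 0.01. The figure near 0.09 needs tests at 0.05, which the article does not state for this outcome. What remains is that the analysis section does not repeat 0.005.

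Third, hypotheses 2 to 4 repeat nearly the same two-visit phrase, so it may only say when effects are expected. That is plausible, but it is still the wording of the main hypothesis.

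Fourth, the chi-square sentence does not mention relapse and could apply at T1, T2 or both. Agreed; that vagueness is part of the conflict.

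Fifth, ranking visits is often left to an analysis plan. An omission would be no finding, but statements that conflict are.

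Finally, the Introduction's main objective runs on to more than relapse: "in the reduction of relapses, as well as the improvement of clinical symptoms, its possible positive impact on functioning and adherence to pharmacological treatment". This is minor, because Study Aim separates main from secondary outcomes.

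**Conclusion.** The point holds as an inconsistency. The article gives three forms of the main relapse comparison: two visits; one Cox-sized variable to 12 months at 0.005; and a chi-square with no visit or level. The main harm comes from the literal *and* in hypothesis 1. Requiring both visits roughly halves power at 0.05 (14% to 24% against 31% to 49%). It all but removes power if relapses before month 5 are excluded (about 1% to 3% against 19% to 29%). Error inflation is a concern only if 0.005 is dropped in the analysis.

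The power figures rest on assumed control relapse of 30% to 50%, constant hazard, 40 per arm with no other losses, and chi-square tests. They illustrate scale and do not predict this trial. Frequent disagreement between visits is likewise conditional on a true effect; with no effect it is uncommon. The conflict itself rests on the text alone.

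**What to change.** - State one primary contrast: EMDR against usual treatment, relapse over follow-up to T2, the variable that the sample-size section sizes.
- Name one analysis for it in Statistical Analysis, consistent with the sizing (which uses Cox regression), and state there the alpha of 0.005 given for the sizing.
- Reword hypothesis 1 so that the T1 relapse comparison is secondary, tested only if the T2 contrast succeeds.
- Reconcile the exclusion of patients who relapse, in Dropouts and Follow-Up, with hypothesis 1 and the intention-to-treat statement, so that it is clear which relapses count and who is in the denominator.
- Optionally, align the main objective in the Introduction with Study Aim.

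The cost is a few sentences, settled before unblinding, with no extra patients. The exclusion rule needs an explicit decision on how these relapses enter the analysis. The price is that a difference seen only at T1 can no longer carry the main claim. These changes do not repair the sample-size figure, which needs its own review.

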MINI, Mini-International Neuropsychiatric Interview; Diagnosis S, Diagnosis Substance; BDI-II, Beck Depression Inventory—II; YMRS, Young Mania Rating Scale; Psychotic S, Psychotic Symptoms; PANSS, Positive and Negative Symptom Scale; GAF, Global Assessment of Functioning Scale.

Quality of life associated with health, cognitive insight and adherence to treatment will be assessed using the following instruments (see **Table 4**):

Standardized Instrument for Evaluating Quality of Life Associated with Health developed by the EuroQol group (EQ-5D): EQ-5D is a standardized instrument developed by the EuroQol Group (58), available in a validated Spanish version (59), which provides a measure of health-related quality of life that can be used in a wide range of health conditions and treatments. It is comprised of five dimensions: mobility, self-care, usual activities, pain/discomfort and anxiety/depression. The total score ranges from 0 to 100, with lower scores indicating a poorer health-related quality of life.Beck Cognitive Insight Scale (BCIS): The BCIS (60), Spanish validated version (61), is a 15-item self-report scale designed to measure the level of awareness of having a mental disorder and the need for treatment. The scale comprises two sub-scales: self-reflectiveness (nine items) and self-certainty (six items), and a composite score of cognitive insight is given by subtracting self-certainty items from those pertaining to self-reflectiveness.Drug Attitude Inventory (DAI-10): The DAI-10 (62), Spanish validated version (63), is a 10-item scale for measuring attitude towards medication, with a total score obtained by summing the 10 items. In items 1, 3, 4, 7, and 10, if the answer is correct the score will be 2 and if it is false will be 1. In the rest of the items the correct ones score 1 and the false ones 2. The total score can oscillate between 10 and 20. There is no cut-off point but the higher the score, the more positive the perceived effect of the medication.

**Table 4 T4:** Quality of life, cognitive insight, and adherence to treatment.

Clinical variable	Measurement interview/self-report	T0 baseline	T1 Post-treatment 6 months	T2 Post-treatment 12 months
Quality life	EQ-5D	x	x	x
Insight	BCIS	x	x	x
Drug attitude	DAI-10	x	x	x

EQ-5D, Standardized Instrument for Evaluating Quality of Life Associated with Health developed by the EuroQol group; BCIS, Beck Cognitive Insight Scale; DAI-10, Drug Attitude Inventory.

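### Hypothesis 4 and the matching secondary outcome claim better medication adherence, but the only instrument assigned to them, the DAI-10, is described in the protocol as an attitude scale

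*Protocol article*

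**What the plan says.** Adherence is a formal claim in the protocol article. Under Hypotheses, the fourth item reads "Patients in the EMDR group will show a better adherence to pharmacological treatment in relation to the control group after therapy (T1"), with the same prediction at T2. Study Aim closes its list of secondary outcomes with "as well as adherence to pharmacological treatment. A range of clinical scales will be used the evaluate changes from baseline" and sends the reader to Instruments and Measures for the scales. The last paragraph of the Introduction includes adherence in the objective, and Statistical Analysis includes it among the characteristics to be described at baseline.

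The instruments are named in two places. The abstract's Methods paragraph says: "The cognitive insight and adherence to the treatment will be assessed with the Beck Cognitive Insight Scale and the Drug Attitude Inventory". Instruments and Measures says: "Quality of life associated with health, cognitive insight and adherence to treatment will be assessed using the following instruments", and then lists the EQ-5D, the BCIS and the DAI-10.

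The DAI-10 itself "is a 10-item scale for measuring attitude towards medication, with a total score obtained by summing the 10 items". Its score is read as follows: "There is no cut-off point but the higher the score, the more positive the perceived effect of the medication".

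**The concern.** The construct named in the hypothesis and the construct that the instrument is said to measure are different. A patient can think well of a medicine and miss doses, or dislike it and take it as prescribed. If the plan is followed as written, a between-arm difference on the DAI-10 is the evidence that would be offered for Hypothesis 4, and an attitude result would carry an adherence label.

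The label matters in this trial. The Introduction says that trauma makes adherence to drug treatment harder and that adherence is already difficult after a first episode. Readers will therefore be inclined to take an adherence finding as part of the account of any reduction in relapses.

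**Working it through.** No sample-size, power or error-rate figure bears on this point. The check sets each instrument that could serve Hypothesis 4 beside the protocol's own description of it.

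**Step 1: the construct.** Hypotheses and Study Aim both name adherence to pharmacological treatment, compared between arms at T1 and T2.

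**Step 2: the instruments assigned to it.** The list in Instruments and Measures that is introduced as covering adherence has three members.

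| Instrument | What the protocol says it measures | Adherence? |
|---|---|---|
| EQ-5D | health-related quality of life, five dimensions | no |
| BCIS | "designed to measure the level of awareness of having a mental disorder and the need for treatment" | no: insight |
| DAI-10 | attitude towards medication; a higher score means a more favourable perceived effect | no: attitude |

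Only the DAI-10 concerns medication, so it carries Hypothesis 4 alone.

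**Step 3: what the score can show.** Ten items are each scored 1 or 2, so the minimum is 10 × 1 = 10 and the maximum is 10 × 2 = 20. This reproduces the stated range of 10 to 20. The protocol gives no cut-off and does not tie any value to medication taking, so the score yields no adherence rate or category.

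**Step 4: Table 4 against itself.** The title names adherence to treatment. The row for the DAI-10 is labelled drug attitude. The two terms are used as if they were interchangeable.

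**Step 5: any other source.** None of Tables 1 to 4 lists a measure of medication taking. Limitations announces a pharmacological treatment variable. It is not defined there, and it is offered to deal with uncontrolled drug treatment as a source of bias, not as the outcome for Hypothesis 4.

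**Step 6: whom the outcome covers.** Inclusion criterion 2 under Participants admits patients with or without pharmacological treatment. Adherence to medication is not defined for a participant who has none prescribed.

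**The case against.** The strongest reply is that this is a naming matter on one secondary scale. The protocol is open about what the DAI-10 measures, the Table 4 row is labelled correctly, and the abstract's numbered objectives and conclusion do not mention adherence. Attitude may also be a reasonable proxy for adherence, and the scale and its Spanish validation are cited. Much of this stands: the reach of the error is limited, and correcting it changes no sample size and no primary analysis. It does not remove the mismatch, because the document never says that the DAI-10 is used as a proxy, gives no reason for such use, and states the hypothesis in terms of adherence.

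A reader might go further in four ways that the documents do not support.

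- *That the relapse result is compromised because an EMDR effect cannot be told apart from a medication-taking effect.* A change in adherence brought about by EMDR after randomisation is a mediator. It is part of the total effect of allocation on relapse, not a confounder, and the protocol states no mediation aim.
- *That the trial collects nothing at all on medication taking.* The pharmacological treatment variable, and the relapse-related factors mentioned under Dropouts and Follow-Up, are not described closely enough to say so. What can be said is that neither is presented as an adherence outcome.
- *That the DAI-10 is self-reported by patients who know their arm.* The article says that patients cannot be masked, but it does not state how the DAI-10 is administered. It calls the BCIS self-report and the DAI-10 only a scale, and the Table 4 column heading covers both modes.
- *That the DAI-10 could never serve as a proxy.* That depends on validation studies that are not at hand.

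**Conclusion.** The point holds as a mismatch stated within the document. It is not a detail left to a fuller protocol or analysis plan, because the article names the construct, names the instrument and describes that instrument as measuring something else. As written, Hypothesis 4 (one of four) and the adherence component of the secondary outcome can be answered only for attitude towards medication, on a scale from 10 to 20.

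The conclusion rests on the protocol's own description of the DAI-10 and on the absence, in its tables and text, of any medication-taking measure designated as an outcome. A full protocol that designated one would answer the point. The primary relapse comparison, the sample size and the other three hypotheses are not affected.

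**What to change.** Restate Hypothesis 4 and the secondary outcome in Study Aim as attitude towards medication (DAI-10). Change the Table 4 title and the matching text in the abstract, Introduction, Instruments and Measures, and Statistical Analysis in the same way. State that no adherence conclusion will be drawn from the DAI-10. This costs only wording: no new instrument, visit or participant.

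If the sponsor wishes to keep an adherence claim, it must rest on a defined measure of medication taking, under three conditions:

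- **Timing:** it is recorded at T0, T1 and T2, since Study Aim refers to change from baseline.
- **Population:** it is limited to participants prescribed medication, with that group defined in advance.
- **Who collects it:** if it comes from treatment charts, someone other than the blinded raters abstracts it. EMDR participants also receive TAU, so a chart may reveal the arm and unblind the clinician-rated scales.

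This second route is not free. It needs an extra data item and a person outside the blinded assessment to collect it.
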